# Statistical methodology

## Data base

The database will be a description of:

- data acquisition platform
- registration and use platform, for analysis
- definition of the structure of the database, if applicable

The database will be rigorously defined with the variables destined to be analyzed according to the objectives set. The necessary information will be exported from the clinical information manager, SIVIS, to a table in Excel format through a database-based query system.

The exported data will be duly codified in order to protect the clinical and personal information of the patients according to the applicable law in the place where the research project is carried out.

Finally, and prior to the statistical study, an exploratory data analysis will be carried out to review the quality of the information extracted.

## Study Variables

### Main-outcome measures (Dependent)

PGT-A:

- Ploidy outcome: euploid or aneuploid

### SECONDARY outcome measures (Dependent)

PGT-A:

- mtDNA copy number (de los Santos et al., 2018):
  - Mitoscore value: represents the normalized mtDNA content in (an)euploid embryos and indicates the total mtDNA content in the sample

Pre-implantation development:

- Number of COCs retrieved
- Maturation rate: number of mature oocytes obtained in each arm
  - ICSI: defined on day 0 as the number of injected oocytes/number of COCs assigned to the ICSI group
  - IVF: defined on day 1 as the number of oocytes with an extruded PB/number of inseminated oocytes
- Fertilization rate: number of zygotes with 2PN/number of oocytes assigned to the group
- Embryo quality on day 3 defined by the Istanbul consensus (Alpha Scientists, 2011)
  - The number of blastomeres and their division pattern, fragmentation, presence of compaction, vacuoles, granulation and nuclei will divide the embryos into 3 categories: good, fair or poor
  - Cell number on day 3 for all fertilized oocytes
- Embryo quality on day 5 (Gardner and Schoolcraft,1999) defined by the Istanbul consensus (Alpha Scientists, 2011)
  - The blastulation rate: number of embryos reaching at least the BL1 stage/ number of oocytes assigned to that group: defined by a 1 (yes, the embryo is blastulating) or 0 (no, the embryo is not blastulating)
  - The expansion stage of the blastocyst and the quality of the ICM and TE will divide the embryos into 3 categories according to Istanbul consensus
- Utilization rate: number of embryos that can be used for the patient (=number of embryos that can be biopsied)/number of oocytes assigned to the group
- Day on which the biopsy is performed (day 5,6 or 7)
- Morphokinetic parameters defined by time lapse imaging starting from the time of syngamy/PN fading (Basile et al., 2014)
  - t2: the timing to two cells
  - t3: the timing to three cells
  - t4: the timing to four cells
  - t5: the timing to five cells
  - t8: the timing to eight cells
  - SC: starting to compact
  - M: the timing to morula
  - SB: starting to blastulate
  - B: reaching a BL3 according to Gardner and Schoolcraft, 1999
  - F: reaching a BL4 according to Gardner and Schoolcraft, 1999
  - cc2: t3-t2
  - s2: t4-t3
- Biopsy yes or no: indicating developmental competence or developmental arrest
- Blastocyst gender: male or female

Clinical cycle outcome:

- Pregnancy (yes or no) defined by a βhCG test of > 15IU
- Biochemical pregnancy (yes or no) defined as a pregnancy in which the hCG levels start do decrease after 1 week
- Implantation rate (%) defined by the number of gestational sacs/number of embryos transferred
- Clinical pregnancy (yes or no) defined by the ultrasonographic visualization of one or more gestational sacs, including ectopic pregnancies

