## Intervention and Follow-up

Couples that are eligible for the study will be selected on the day of OPU based on all inclusion and exclusion criteria (as described under “D. Subject inclusion/exclusion criteria”) and will be asked to participate in the study by signing the IC. A randomization list will determine to which group the first half (or one extra in case an odd number is available) of the oocytes will be assigned. As to prevent selection bias, oocytes will be assigned to both groups under low magnification and different cumulus expansion stages will be evenly divided. Oocytes selected for ICSI will be denuded and injected on the day of OPU after which their pre-implantation development will be followed by time lapse imaging. IVF oocytes will be inseminated (individual or per two) overnight with 10.000 PR sperm cells in a G185 incubator (K systems) and denuded in the morning of day 1 after which they will be transferred to the time lapse imaging incubator. Blastocysts of sufficient quality (to determine this, morphokinetic parameters shall be measured) will be biopsied on day 5-7 after which the blastocysts are vitrified individually. PGT-A (NGS platform) is performed on all TE biopsy samples and the ploidy state and mtDNA score will be provided. All annotated time lapse imaging data will be gathered and combined with the pre-implantation data, PGT-A data (ploidy state and mtDNA copy number) and all general patient and cycle characteristics. Patients with euploid embryos available will receive a FET and implantation rates and (clinical) pregnancy outcomes will be recorded.

The follow-up of the patients does not deviate from a normal fertility trajectory.

Quantification of the determining variables:

The primary outcome variable is the ploidy state

Secondary outcome variables are the (i) embryo development defined by the number of COCs retrieved, maturation and fertilization rate, embryo development analysed on day 3 and day 5, total number of embryos used for the patient, day of biopsy and the morphokinetic parameters; (ii) mtDNA copy number and (iii) the clinical outcome.

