### Objectives assessment

Main objective

In order to compare the effect of IVF versus ICSI on the blastocyst ploidy state a Poisson regression will be performed, which is the most appropriate statistical modelling method to analyse count data.

Secondary objectives

To compare IVF versus ICSI outcomes in preimplantation development outcomes:

- To compare the maturation rate, a t-test will be used to detect differences in the average number of mature oocytes (a Wilcoxon test will be used if we cannot assume normal distribution of data). If we found differences, linear or Poisson regressions will be performed to evaluate them in a model taking into account rest of explanatory variables.
- To compare the fertilization rate, a t-test will be used to detect differences in the average number of zygotes with 2PN oocytes (a Wilcoxon test will be used if we cannot assume normal distribution of data). If we found differences, linear or Poisson regression will be performed to evaluate them in a model taking into account rest of explanatory variables.
- In order to compare embryo quality on D3 (measured using the Istanbul consensus), a multinomial logistic regression will be performed.
- Embryo quality D5
  - To compare the blastulation rate, a t-test will be used to detect differences in the average number of embryos reaching at least the BL1 stage (a Wilcoxon test will be used if we cannot assume normal distribution of data). If we found differences, linear or Poisson regressions will be performed to evaluate them in a model taking into account rest of explanatory variables.
  - In order to compare embryo quality on D5 (The expansion stage of the blastocyst and the quality of the ICM and TE will divide the embryos into 3 categories), a multinomial logistic regression will be performed.
- To compare the utilization rate, a t-test will be used to detect differences in the number of embryos that can be used for the patient (a Wilcoxon test will be used if we cannot assume normal distribution of data). If we found differences, linear or Poisson regressions will be performed to evaluate them in a model taking into account rest of explanatory variables.

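### Maturation is read on day 0 as injected oocytes in ICSI and on day 1 as extruded polar bodies in IVF, yet the arms are tested against each other

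*Protocol*

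**What the plan says.** The same maturation definitions appear in the protocol under Secondary Objectives/research questions and under SECONDARY outcome measures (Dependent). One arm is read on the day of retrieval: "ICSI: defined on day 0 as the number of injected oocytes/number of COCs assigned to the ICSI group". The other arm is read a day later and with a different numerator: "IVF: defined on day 1 as the number of oocytes with an extruded PB/number of inseminated oocytes".

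Intervention and Follow-up shows why they differ. "Oocytes selected for ICSI will be denuded and injected on the day of OPU", whereas the IVF oocytes stay with the sperm overnight and are "denuded in the morning of day 1 after which they will be transferred to the time lapse imaging incubator". Maturity cannot be read until the cumulus is removed, and that happens a day later in IVF.

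Objectives assessment then tests the arms against each other: "To compare the maturation rate, a t-test will be used to detect differences in the average number of mature oocytes", with a Wilcoxon test if normality cannot be assumed. Pairing within couples is not stated. If a difference is found, a linear or Poisson regression on the other explanatory variables follows.

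Two further provisions matter. A randomization list decides which arm receives the first half of the oocytes, and this is done before denudation. The exclusion criteria remove a couple if denudation in the ICSI arm yields only 2 mature oocytes; the IVF arm has no counterpart.

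**The concern.** Allocation precedes denudation and insemination, so the share of oocytes mature at retrieval is equal in expectation in the two arms. The planned test nevertheless compares two different quantities, for two reasons:

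- **Reading day.** An oocyte that is immature on day 0 and extrudes its polar body overnight counts as mature in IVF. In ICSI the count has already closed.
- **Numerator.** ICSI counts injected oocytes and IVF counts oocytes with a polar body. A mature oocyte that is not injected is lost from the ICSI count only.

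The follow-on regression cannot repair this. Reading day coincides exactly with arm, and no listed explanatory variable separates the two.

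A measurement difference could therefore be reported as an effect of the insemination method. This matters even in a pilot. The section Sample Size says the estimates will serve to plan a later study, and the Justification states an aim in favour of IVF.

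**Working it through.** The protocol gives no maturation rate, significance level or power to reproduce, so this is an illustration.

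**Inputs from the protocol.** There are 30 couples (Sample Size) and at least 10 COCs per couple, split in half, which gives at least 5 per arm.

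**Assumptions not in the protocol.** Day-0 maturity p is 0.75 in both arms. The share m of immature oocytes that mature before the day-1 reading is 0.10 to 0.40. The test is two-sided at 5%. Maturity varies between couples by a beta distribution with within-couple correlation of about 0.05. The exclusion is read as two or fewer mature ICSI oocytes, and excluded couples are replaced to reach 30.

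**Step 1: timing artefact before the exclusion.** The spurious IVF excess is m × (1 − p).

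- m = 0.10: 0.10 × 0.25 = 2.5 points
- m = 0.20: 0.20 × 0.25 = 5 points
- m = 0.30: 0.30 × 0.25 = 7.5 points
- m = 0.40: 0.40 × 0.25 = 10 points

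**Step 2: effect of the ICSI-only exclusion.** Keeping only couples with three or more mature ICSI oocytes, with m = 0, the simulation puts ICSI above IVF by e = 4.7 points at 5 oocytes per arm and e = 0.6 points at 8. In the couples kept, day-0 maturity q in the IVF arm is 76.1% and 75.2% respectively.

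**Step 3: net difference.** Net = m × (1 − q) − e. For example, at 5 per arm and m = 0.10, 0.10 × 23.9 − 4.7 = −2.3 points. At m = 0.40 it is 0.40 × 23.9 − 4.7 = +4.9 points. At 8 per arm and m = 0.40 it is 0.40 × 24.8 − 0.6 = +9.3 points.

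**Step 4: chance that a paired t-test in 30 couples gives p < 0.05 with no true effect** (simulated; repeat runs differ by a point or two).

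| m | Net, 5 per arm | Rejects | Net, 8 per arm | Rejects |
|---|---|---|---|---|
| 0.10 | −2.3 points | 7% | +1.9 points | 7–8% |
| 0.20 | +0.1 points | 5% | +4.4 points | 21–22% |
| 0.30 | +2.5 points | 10–11% | +6.8 points | 46–47% |
| 0.40 | +4.9 points | 24–26% | +9.3 points | 73% |

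**Step 5: sensitivity to the test.** The protocol tests counts and does not state pairing. If COCs vary from 10 to 25 per couple, an unpaired t-test on counts, before the exclusion, rejects in only about 2%, 7% and 18% of trials at m = 0.20, 0.30 and 0.40. Variation in cohort size between couples then swamps the artefact. The bias in the estimate remains; it is only less likely to reach significance.

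**Check.** With m = 0 and no exclusion the difference is 0 points, and the paired test rejects in about 5% of trials, as it should.

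**The case against.** The strongest reply has four parts.

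*The reading days are stated openly and follow from the procedure.* This is true. IVF oocytes are not denuded until day 1, so a common reading day is not available within this plan. That explains the two definitions but does not justify testing one against the other.

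*Direction and size are not established.* This stands. A reader might infer that the plan will show a spuriously higher maturation rate with IVF. The documents do not support so firm a statement: the ICSI-only exclusion raises the ICSI rate, and in small cohorts it can cancel or reverse the artefact. The overnight maturation rate is not given, and at its low end the rejection rate is near nominal. Two opposing artefacts of unknown size still leave the p-value without a clear meaning.

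*Day-3 and day-5 scores are a different matter.* This also stands. A reader might infer that these scores share the fault, since fertilization starts by injection in one arm and by overnight insemination in the other. Yet both arms are scored on the same named day, and the protocol gives no clock times from which a lag could be derived. Developmental status on a given day is a legitimate outcome of a method. Age-aligned development is covered separately: "Morphokinetic parameters defined by time lapse imaging starting from the time of syngamy/PN fading".

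*This is one secondary outcome in an unpowered pilot.* That is correct and limits the weight of the point.

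**Conclusion.** The point holds for maturation only. The protocol itself fixes two different readings and a direct test between them, so this is not a detail left to a later analysis plan. Under equal true maturity, that test can reject because of when and how maturity was counted.

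If day-0 maturity is 75% and 10–40% of immature oocytes mature overnight, the timing artefact is 2.5–10 points towards IVF before the exclusion. With the exclusion read as two or fewer mature oocytes, the net is about −2 to +5 points at 5 oocytes per arm and +2 to +9 points at 8. Paired rejection rates are about 5–26% and 7–73%; an unpaired test on counts rejects less often. All these figures rest on assumed rates, so they show that the problem can be material, not how large it will be.

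It would be wrong to extend this to the main result: the primary ploidy comparison does not use maturation.

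**What to change.** - In Objectives assessment, remove the between-arm test of maturation and the regression that depends on it.
- Report maturation descriptively in each arm, stating the reading day and the numerator beside each figure.
- Treat fertilization per oocyte assigned as the earliest comparative developmental outcome. Its numerator (2PN zygotes) and denominator (oocytes assigned) are already the same in both arms.
- Report how many couples were excluded for low ICSI-arm maturity. That rule selects on one arm and so still bears on other between-arm comparisons, including fertilization.

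The cost is a change of wording and the loss of one secondary p-value. No extra culture, imaging or patients are needed, and the scoring on day 3 and day 5 need not change on this account.

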### explanatory variables (INDEPENDENT)

Principal exposure factor

- Intervention: IVF or ICSI

Patient and cycle characteristics

- Sperm parameters before and after capacitation:
  - Concentration
  - PR
- BMI (kg/m^2^)
- Female age at the moment of OPU (years)
- AMH
- Smoking habit
  - Not smoking: 0
  - Smoking: 1
- Race
- Hormones on the day of trigger
  - E_2_ (pg/ml)
  - P (ng/ml)
- Ovarian stimulation
  - Ovarian stimulation protocol
  - Total dose of gonadotrophins used (IU)
  - Duration of stimulation (days)
- Trigger
  - Type
  - Units (IU)
- Abstinence duration
- Indication for PGT-A testing
- Endometrial preparation for FET
- Primary or secondary infertility

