# Abstract

ICSI is commonly used in PGT cases to eliminate any risk of sperm DNA contamination. With the switch from cleavage stage biopsy to biopsy of the full (hatching) blastocyst, this potential risk of contamination can be neglected and could allow the use of conventional IVF in PGT cases. Especially in cases of non-male factor infertility, the use of conventional IVF can be applied as a more ‘natural’ insemination method.

A pilot study will be performed on sibling oocytes including patients with non-male factor infertility and requesting PGT-A (NGS platform). If at least 10 cumulus oocyte complexes (COCs) are obtained after oocyte retrieval, half of the oocytes will be subjected to ICSI and the other half to conventional IVF. Preimplantation development is followed by time lapse imaging and blastocysts (day 5-7) fulfilling the biopsy criteria will undergo trophectoderm biopsy to detect the ploidy state and the mtDNA copy number.

The main objective is to analyse if the use a more physiological insemination method (IVF) has a beneficial impact on the ploidy state of the blastocyst as compared to ICSI within the same patient. As the embryos will be cultured in a time lapse imaging system, annotations can be made and the differences in maturation rate, fertilization rate and embryo development between both insemination methods can be analysed as secondary outcome parameter. On top of this, the PGT-A outcome will also display the mtDNA copy number which can be compared between IVF and ICSI biopsied sibling blastocyst. Euploid blastocysts will be transferred in subsequent FET cycles and give an indication on the clinical outcome between IVF and ICSI.

Would this study enable us to undermine the dogma to perform ICSI for all PGT cycles?

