- In order to evaluate morphokinetic parameters defined by time-lapse imaging starting from the time of syngamy and their effect on ploidy, biopsy day, embryo arrest and gender, first we will present a trend chart to describe the average development times of the embryos according to the treatment. Then, growth models (linear or exponential) will be performed for each embryo, to estimate a growth parameter that can be compared between IVF and ICSI treatments.

To compare IVF versus ICSI outcomes in mtDNA:

- A t-test will be used to detect differences in the Mitoscore value depending on the treatment (IVF or ICSI) if we can assume normality distribution for Mitoscore value (in other case, a Wilcoxon test will be performed). Moreover, linear regression models will be performed to analyse the treatment effect in the presence of the remaining covariates.

To compare IVF versus ICSI outcomes in cycle outcomes:

- We will build a contingency table, and then, a chi-squared test will be used in order to compare the pregnancy, biochemical pregnancy, and clinical pregnancy results between IVF versus ICSI treatments. If we found statistical differences, a logistic regression will be performed to evaluate this differences in a model taking into account rest of explanatory variables.
- To compare the implantation rate, a t-test will be used to detect differences in this rate (a Wilcoxon test will be used if we cannot assume normal distribution of data). If we found differences, linear or Poisson regressions will be performed to evaluate them in a model taking into account rest of explanatory variables.

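### Endometrial preparation for FET is listed as a covariate for every outcome, but for Mitoscore and the four laboratory rates it arises after the outcome and only in couples with a euploid embryo

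*Protocol*

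**What the plan says.** The protocol's section on explanatory (independent) variables names the insemination method as principal exposure and then gives a single list of patient and cycle characteristics. One entry is "Endometrial preparation for FET". No entry is reserved for particular outcomes.

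The Objectives assessment section draws on that list as follows:

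- **Mitoscore.** After a t-test or Wilcoxon test, "linear regression models will be performed to analyse the treatment effect in the presence of the remaining covariates". No condition is attached.
- **Maturation, fertilization, blastulation and utilization.** An unadjusted test comes first. For maturation, blastulation and utilization the text then reads "If we found differences, linear or Poisson regressions will be performed to evaluate them in a model taking into account rest of explanatory variables"; for fertilization the wording is nearly the same.
- **Pregnancy outcomes.** If the chi-squared test shows a difference, "a logistic regression will be performed to evaluate this differences in a model taking into account rest of explanatory variables". Implantation rate has a similar rule.
- **Ploidy (primary), day-3 and day-5 quality, morphokinetics.** A Poisson regression, multinomial regressions and growth models respectively. None of these names a covariate.

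On who has a transfer, and when, Intervention and Follow-up says "Patients with euploid embryos available will receive a FET", after biopsy, vitrification and PGT-A. The Abstract says "Euploid blastocysts will be transferred in subsequent FET cycles".

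**The concern.** A covariate in a model for a laboratory outcome should be settled before that outcome. Endometrial preparation belongs to a later transfer cycle, so it cannot explain maturation, fertilization, blastulation, utilization or mtDNA content. Under the protocol's own transfer rule it has a value only if the couple obtained a euploid embryo. That depends on how many oocytes became biopsied blastocysts, which is the utilization outcome, and on their ploidy.

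The protocol does not say how a couple without a transfer is coded, and neither obvious choice is neutral. If the field is blank, a complete-case regression drops the couple. If it holds a category such as *none*, the model adjusts for a marker of having no euploid embryo, or no transfer yet.

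What is at stake is the adjusted secondary results. Sample Size says the pilot should supply statistical parameters for a later study. Parameters taken from models fitted only to couples with a euploid embryo would describe a selected group. For Mitoscore, the Background itself reports that ploidy state has been found to affect mtDNA copy number, so the selection acts on something linked to the outcome.

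**Working it through.** The 30 couples are a feasibility choice without a power calculation, so there is no stated figure to reproduce. The check has a textual part and an illustrative part.

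**Which models are reached**

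| Model | Covariates stated | When run | Is endometrial preparation fixed before the outcome? |
|---|---|---|---|
| Mitoscore | all remaining | always | no |
| Maturation, fertilization, blastulation, utilization | all remaining | if a difference is found | no |
| Pregnancy outcomes, implantation | all remaining | if a difference is found | yes, and defined for every transfer |
| Ploidy, day-3/day-5 quality, morphokinetics | none | always | not applicable |

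The problem is confined to the first two rows.

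**How many couples have no value**

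From the protocol: 30 couples and at least 10 oocyte complexes per couple, so n = 5 per arm at the minimum. Assumed, because the protocol gives neither: u = biopsied blastocysts per assigned oocyte complex, and e = euploid share of biopsied blastocysts.

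With independent oocytes, P(no euploid embryo) = (1 − u·e)^(2n).

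- Central, u = 0.30, e = 0.45: 0.865^10 = 0.235, or 7.0 of 30.
- Favourable, u = 0.40, e = 0.60: 0.76^10 = 0.064, or 1.9 of 30.
- Unfavourable, u = 0.20, e = 0.30: 0.94^10 = 0.539, or 16.2 of 30.

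With n = 7 per arm the same three cases give 3.9, 0.6 and 12.6 of 30. Letting couples differ (logit SD 0.8, assumed, n = 5) raises the central case to about 9 of 30.

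**How many blastocysts are lost for Mitoscore**

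Couples without a euploid embryo have fewer blastocysts. The share of blastocysts lost is (1 − e)(1 − u·e)^(2n−1):

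- Central: 0.55 × 0.865^9 = 0.149, against 23.5% of couples.
- Favourable: 0.40 × 0.76^9 = 0.034, against 6.4%.
- Unfavourable: 0.70 × 0.94^9 = 0.401, against 53.9%.

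**Precision**

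If the standard error scales with one over the square root of the units kept, the central case inflates it by 1/√(1 − 0.235) = 1.14 for a couple-level rate, and by 1/√(1 − 0.149) = 1.08 for Mitoscore with blastocysts treated as independent. The corresponding ranges are 1.03 to 1.47 and 1.02 to 1.29.

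**Levels and contrast when couples without a euploid embryo are dropped** (simulation, n = 5, logit SD 0.8)

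| Assumed inputs | Couples dropped of 30 | Utilization, all couples → kept | Utilization ratio between arms, true → kept |
|---|---|---|---|
| u 0.30; e 0.45 in both arms | about 9 | 0.32 → 0.39 | 1.00 → 1.00 |
| u 0.30; e 0.35 vs 0.50 | 9 to 10 | 0.32 → 0.38 and 0.40 | 1.00 → 0.97 |
| u 0.20; e 0.25 vs 0.40 | about 15 | 0.23 → 0.31 and 0.33 | 1.00 → 0.93 |

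In the first row the euploid share of blastocysts rises from about 0.46 to 0.54 in both arms. Levels shift, but with no arm difference the contrast does not, because retention depends on a euploid embryo from either arm and applies to both sibling arms alike.

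**If *none* is used as a category instead**

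No couple is lost. In a linear model with one row per couple and arm, a covariate shared by both arms is balanced between them, so it leaves the estimated rate difference unchanged. Mitoscore is measured per embryo and couples contribute unequal numbers to the two arms, so there the adjustment can move the estimate.

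**The case against.** The strongest reply is that the list is an inventory for all objectives, the cycle outcomes included, where endometrial preparation is a proper covariate. Race is also listed although inclusion is limited to an Arab population, which suggests an inventory rather than a set to be forced whole into every model. Assigning covariates to models and handling inapplicable values is commonly left to a statistical analysis plan, which may exist but is not shown. Complete-case deletion and a *none* category are assumptions about software and coding; the protocol states neither.

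This softens the point but does not remove it. The protocol does more than list variables. It instructs that the remaining ones enter the models, in the same kind of wording for laboratory and pregnancy outcomes. An analysis plan that followed it faithfully would carry the error forward.

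Other parts of the reply stand in full. The unadjusted tests come first and use all couples with data. The four rate models may never be fitted. All the drop-out figures rest on assumed rates.

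Two stronger readings are tempting. A reader might infer that the primary analysis is conditioned on its own result. The text does not support this: the Poisson model for ploidy names no covariates, and the same holds for the embryo-quality and morphokinetic models. A reader might also infer that the IVF-ICSI comparison is seriously biased. The selection is that the couple has at least one euploid embryo, not the ploidy of each embryo, and both sibling arms share it. The contrast therefore moves little in the cases examined.

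**Conclusion.** The protocol is wrong as written on a limited point. It puts a covariate that comes after the outcome, and depends on the result, into one secondary model that is always run (Mitoscore) and four that are conditional (maturation, fertilization, blastulation, utilization). It is properly placed only in the cycle-outcome models.

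At the minimum of 10 oocyte complexes per couple, roughly 2 to 16 of 30 couples would leave a complete-case fit, centrally 7 to 9; with more oocytes the number falls. The share of blastocysts lost for Mitoscore is smaller than the share of couples. Without a true arm difference the contrast is unbiased. With one, the utilization ratio moved from 1.00 to 0.97 in the milder case, and to 0.93 where about half the couples were lost. The main harm is lost precision and a selected population.

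The direction follows from the text; the sizes rest on assumed biopsy and euploidy rates and assumed variation between couples. Mitoscore bias itself was not simulated. Severity is minor.

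**What to change.** Make two wording changes in the protocol.

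1. In the list of explanatory variables, mark endometrial preparation as applying only to the clinical cycle outcomes.
2. In Objectives assessment, for maturation, fertilization, blastulation, utilization and Mitoscore only, replace the open reference to all remaining variables with *explanatory variables fixed before insemination*.

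Leave the ploidy, embryo-quality and morphokinetic analyses alone on this point. They name no covariates, and extending the wording to them would introduce an adjustment that the protocol does not now plan.

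No extra data, couples or procedures are needed. With the change, no couple leaves these models because of this variable.
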